### Health behaviors and health outcomes

All outcomes will be measured in the intervention and control groups at baseline and 1, 3, 6, and 12 months. Demographic characteristics (age, gender) and treatment group (IHD, valve disease or arrhythmia) will be obtained from medical record.

Other outcomes will be obtained patient reported in REDCap. The primary outcome of interest, loneliness, is measured with HiRL tool [10]. The secondary outcome of interest is measured with the following questionnaires: Self-care: Self Care Self-Efficacy scale (Cronbach’s alpha 0.93) [40], health-related quality of life (HeartQoL) (Cronbach's alpha ≥ 0.80) [41], and Hospital Anxiety and Depression scale (HADS) [42] (in cardiac patients: Cronbach’s alpha 0.87 for HADS-A and 0.82 for HADS-D) [43]. Measures on health behaviors, i.e., smoking, alcohol consumption, weight, physical activity, and participation in cardiac rehabilitation, will be patient reported. An overview of outcome measurements and related measurement tools is presented in Fig. 2.

**Fig. 2 Fig2:**
[figure not shown]
Schedule of enrollment, interventions, and data collection

## Data analysis

As recommended for the analysis of pilot studies [44], descriptive statistics will be presented as mean and standard deviations (SD) for continuous variables and frequencies and percentages for categorical variables at baseline and follow-ups (1, 3, 6, and 12 months).

To examine the comparability of the intervention group and the control group, baseline characteristics of the groups will be compared using Pearson’s chi-square or Fisher’s exact test for categorical variables and a *t*-test or Mann–Whitney test for continuous variables. Similar descriptive comparison of health outcome variables by group will be performed at follow-ups. The primary analyses will be performed according to the intention-to-treat principle.

To improve statistical efficiency, the primary outcome, i.e., loneliness, will be analyzed with a regression model adjusted for the stratification variables and the baseline variables, as recommended by the American Medical Association [45] and the European Medicines Agency [46].

Note, we do not aim to investigate statistically significant differences between groups as this is a feasibility trial. Therefore, no power calculation will be conducted. Rather, the measurement of health behaviors and health outcomes aims to give an indication of the potential variability in the outcome measures, which will be used to inform the power calculation for a future RCT.

A lost to follow-up analysis will be conducted for gender, age (higher or lower than mean), treatment procedure, and type of informal caregiver.

All statistical analyses will be performed using SAS Enterprise 7.1.

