## Study aims and objectives

The primary aim of the study is to determine the feasibility of an individually structured social support intervention targeting patients treated for cardiac disease who experience loneliness.

The secondary aim is to explore the preliminary evidence on the effect of the intervention on health behaviors and health outcomes. The results will be used to perform a sample size calculation in a potential future larger trial [26].

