## Trial design

A feasibility study based on randomized clinical trial (RCT) design. The RCT design with 1:1 randomization to a 6-month social support program, plus usual care (intervention) versus usual care, (i.e., regular guidelines-based follow-up [29], will provide preliminary evidence on the effect of the intervention on patient-reported outcomes, health behaviors, and health outcomes. To investigate the sustainability of a potential long-term effect of the intervention, the follow-up period will be 1 year.

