### Sample size

As the primary aim of this study is to test feasibility, there is no requirement for a formal power calculation [30]. Considerations about the sample size are related to the fact that no previous studies have investigated a social support intervention targeting patients with cardiac disease who experience loneliness and, therefore, no data exists on acceptability to the intervention. A sample size of 40 was chosen as it seems reasonable to exploratory investigate the feasibility, in particular acceptability, in a small sample and at the same time have a sample size big enough to investigate the additional aspects that are being assessed for feasibility [31]. Consequently, the study will include 20 patients and 20 informal caregivers in the intervention group and 20 patients in the control group. A flowchart of the trial is presented in Fig. 1.

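### Baseline and gender adjustment is specified for loneliness only; the continuous secondary outcomes are compared unadjusted, which costs precision but does not cause bias

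*Protocol article*

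**What the plan says.** Three statements in the protocol article matter here.

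- **Data collection** (Health behaviors and health outcomes): "All outcomes will be measured in the intervention and control groups at baseline and 1, 3, 6, and 12 months". Besides loneliness, these include the Self Care Self-Efficacy scale, HeartQoL, the two HADS subscales and self-reported weight.
- **Loneliness** (Data analysis): "the primary outcome, i.e., loneliness, will be analyzed with a regression model adjusted for the stratification variables and the baseline variables". The stated reason is efficiency, and guidance recommending such adjustment is cited.
- **Other outcomes** (Data analysis): "Similar descriptive comparison of health outcome variables by group will be performed at follow-ups". The sentence before it says that "baseline characteristics of the groups will be compared using" two-group tests: t or Mann–Whitney if the variable is continuous, chi-square or Fisher if it is categorical. None of these takes a covariate, and no other section gives the secondary outcomes an adjusted model or a change-score analysis.

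On purpose, the secondary aim (Study aims and objectives) is to "explore the preliminary evidence on the effect of the intervention on health behaviors and health outcomes". The Data analysis section adds that statistical significance is not sought and that the observed variability is meant for planning a later trial.

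**The concern.** The article accepts the argument for adjustment but applies it where it can gain little. Under Table 1 each of the two HiRL questions contributes at most one point and entry needs at least one, so a randomized patient's screening score can only be 1 or 2 and the high-risk classification is the same for everyone. The multi-item scales and weight have room to vary at baseline and will usually be correlated with their later values, but they get no adjustment, not even for gender, the stratification factor.

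Two stated purposes are affected. The preliminary effect estimates will be less precise than the same data allow, and part of any chance baseline difference will carry into the follow-up contrast. The planned output, means and SDs by visit, also leaves out the correlation and the residual SD. A future trial that adjusts for baseline, as the cited guidance favors, would need one of these in addition to the raw SD.

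**Working it through.** The article has no power calculation to reproduce ("no power calculation will be conducted"). The check therefore asks what adjustment would gain at the planned size.

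**Inputs**
- 20 patients per arm, from Sample size: "the study will include 20 patients and 20 informal caregivers in the intervention group and 20 patients in the control group". Allocation is equal, from Trial design: "1:1 randomization to a 6-month social support program".
- 15 per arm as a low case: Table 3 tolerates 25% of patients not completing, and 20 × 0.75 = 15.
- Correlation r between baseline and follow-up: not given. Assumed 0.3, 0.5 and 0.7.
- All results are in units of the outcome SD.

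**Step 1: chance baseline imbalance.** SE of the baseline difference = √(2/20) = 0.316 SD. From the normal distribution, an imbalance above 0.3 SD in either direction has probability 0.34, and above 0.5 SD, 0.11. An unadjusted follow-up contrast carries on average r times the imbalance. For 0.3 SD that is 0.3 × 0.3 = 0.09, 0.3 × 0.5 = 0.15 or 0.3 × 0.7 = 0.21 SD.

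**Step 2: gain from adjustment.** ANCOVA multiplies the variance by 1 − r², so SE = √(2/n) × √(1 − r²). The 95% half-width is 1.96 × SE, and the equivalent unadjusted sample is 20/(1 − r²) per arm.

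| r | 1 − r² | SE, n = 20 | Half-width, n = 20 | Equivalent n per arm | Half-width, n = 15 |
|---|---|---|---|---|---|
| unadjusted | 1.00 | 0.316 | 0.62 | 20 | 0.72 |
| 0.3 | 0.91 | 0.302 | 0.59 | 22 | 0.68 |
| 0.5 | 0.75 | 0.274 | 0.54 | 27 | 0.62 |
| 0.7 | 0.51 | 0.226 | 0.44 | 39 | 0.51 |

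**Step 3: does the gain survive a small sample?** Estimating the baseline slope uses some information. In 10,000 simulated trials with 20 per arm, fitting arm and baseline, the ratio of adjusted to unadjusted variance was 0.93, 0.77 and 0.53 for r = 0.3, 0.5 and 0.7. The reductions are thus about 7%, 23% and 47%, slightly below the theoretical 9%, 25% and 51%. A gender term, not included in the simulation, uses one more degree of freedom.

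**Step 4: use in planning.** As an illustration, take a future trial with a difference of 0.3 SD, two-sided 5% and 80% power. Then n per arm = 2 × (1.960 + 0.842)² × (1 − r²)/0.3². With the raw SD (r = 0) this gives 175. With the residual SD it gives 159, 131 or 89 for r = 0.3, 0.5 or 0.7. The raw SD alone cannot show where in that range a baseline-adjusted trial would fall.

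**The case against.** The best defense is the trial's purpose. Feasibility is judged on acceptability and adherence, and no feasibility criterion depends on a HADS or HeartQoL contrast. The comparisons are labeled descriptive. Modeling the primary outcome of interest and describing the rest is a coherent choice with 40 patients, and a fuller analysis plan, not shown here, may add models. The gain also depends on an unknown correlation: at 0.3 the half-width moves only from 0.62 to 0.59 SD.

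Much of this stands, and it limits the weight of the point. It does not remove it. The article states a method for these outcomes rather than staying silent, its own secondary aim includes effects on them, and feasibility status did not prevent adjustment for loneliness.

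A reader might infer more than the article supports:
- *That baseline values are discarded.* They are tabulated at every time point and baseline characteristics are compared by group, so an imbalance would be visible. They are only left out of the follow-up contrasts.
- *That comparisons are restricted to patients who respond.* The article does not say so. It names intention to treat for the primary analyses and plans a loss to follow-up analysis.
- *That the raw SD is the wrong planning input.* It is needed, since residual SD = SD × √(1 − r²). Used alone, it gives a conservative sample size, not an invalid one.
- *That baseline adjustment is pointless for loneliness.* The score can still be 1 or 2, and the model refers to baseline variables in the plural.
- *That a full repeated-measures model is required.* Arm by visit (8), baseline by visit (4) and gender (1) make 13 mean parameters over four follow-ups, and an unstructured covariance adds 10. That is heavy for 40 patients, or 30 at the tolerated loss.

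**Conclusion.** The point holds as a matter of efficiency. The article specifies adjustment for loneliness, where baseline variation is small, and unadjusted comparisons for the continuous secondary outcomes, whose baselines are collected. No test is invalidated and no feasibility conclusion changes.

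The size runs from minor at r = 0.3 to substantial at r = 0.7, where the variance is roughly halved. The conclusion rests on three assumptions: the range of r; the reading that the word similar in the follow-up sentence refers to the tests just named, since the article never uses the word unadjusted; and the inclusion of weight, listed among health behaviors, in that comparison. The point does not extend to items such as participation in cardiac rehabilitation, for which a baseline covariate means little. It is worth changing, but not a condition for running the trial.

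**What to change.** In Data analysis, or in the analysis plan, add the following for self-efficacy, HeartQoL, HADS-A, HADS-D and weight:

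1. At each follow-up visit, report the mean difference between arms adjusted for the outcome's own baseline value and for gender, with a 95% confidence interval. One ANCOVA per visit is enough. A repeated-measures model with a simple covariance structure is an alternative if it converges.
2. Report the baseline to follow-up correlation and the residual SD next to the raw SD, so that the future power calculation can use either.
3. Keep these results descriptive, with no significance claim.

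The cost is a few lines of analysis code and one extra table. No new data, visits or patients are needed.

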## Trial population, eligibility criteria, and randomization

### Patients

Inclusion criteria: Three treatment groups, IHD (CABG or PCI), valve disease (TAVR, SAVR, surgical mitral valve procedures), and arrhythmia (ICD, pacemaker implantation or ablation) treated at Rigshospitalet and classified as high risk lonely according to the High Risk Loneliness (HiRL) tool [10], are given oral and written information about the study design and asked for permission to be contacted within 1 week from discharge to home. The HiRL screening tool has not yet been validated, but previous research suggest that the tool has a prognostic value for 1-year mortality, i.e., sensitivity 19.9% and specificity 89.5%, in patients treated for IHD. The HiRL screening tool is presented in Table 1. The final decision on participation must be taken by the patient within one week of discharge and patients will sign informed consent.

**Table 1 Tab1:** High Risk Loneliness (HiRL) screening tool

Screening question	Answer	Point	Classification of high-risk loneliness
“Does it ever happen that you are alone even though you wish to be with others?”	No		≥ 1 point
	Yes, but rarely		
	Yes, sometimes		
	Yes, often	1	
“Do you have someone to talk to if you experience problems or need support?”	Yes, often		
	Yes, most of the time		
	Yes, sometimes		
	No, never or almost never	1	

Exclusion criteria: Patients who are unable to provide written consent; thus, patients with severe cognitive or physical dysfunction will not be approached.

Randomization: Patients will be identified and screened consecutively. Randomization is completed using the web-based tool Randomizer for Clinical Trials. Patients will be stratified according to gender.

Patients who accept participation and who are included in the intervention group will receive further oral and written information about the intervention structure and sign informed content. In relation to this, they will be asked about their preference for the choice of an informal caregiver and for the structure of the intervention.

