Loss to follow-up	• Percentage of patients and informal caregivers who do not complete the trial	A maximum of 25% of informal caregivers do not attend two out of three intervention consultations with the trial staff attend A maximum of 25% of patients do not complete the trial
Resource consumption	• Time resources used to include study participants • Time resources used to complete the three nurse consultations	N/A for feasibility

In feasibility and pilot testing, it is furthermore recommended that the resources used to complete the study is monitored [30]. This will be done by keeping a record of time resources used to include study participants and to complete the four nurse consultations (enrollment, 1 month, 3 and 6 months) and also frequency and time used on the additional questions from patients and informal caregivers to the open hotline.

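### The loss-to-follow-up analysis splits age at the sample mean without need, and its treatment factor does not match the treatment variable named elsewhere in the article

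*Protocol article*

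**What the plan says.** The Data analysis section fixes the factors of the attrition analysis and the coding of one of them: "A lost to follow-up analysis will be conducted for gender, age (higher or lower than mean), treatment procedure, and type of informal caregiver". It names no test for this analysis.

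Three other places bear on the point.

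- For the comparison of the two arms at baseline, the same section plans "a *t*-test or Mann–Whitney test for continuous variables", and it summarises continuous variables by mean and SD.
- Under Health behaviors and health outcomes: "Demographic characteristics (age, gender) and treatment group (IHD, valve disease or arrhythmia) will be obtained from medical record".
- The patient inclusion criteria place eight procedures within those three groups: "IHD (CABG or PCI), valve disease (TAVR, SAVR, surgical mitral valve procedures), and arrhythmia (ICD, pacemaker implantation or ablation".

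On size, the Sample size section says that "the study will include 20 patients and 20 informal caregivers in the intervention group and 20 patients in the control group", and the feasibility table sets this limit: "A maximum of 25% of patients do not complete the trial".

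**The concern.** Two things in that sentence look badly fixed.

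The first is age. It is available as a number, and the section has a standard way of handling numbers, yet here it becomes above or below the mean. That cut is not known until enrolment is complete, has no stated clinical meaning, and would fall elsewhere in another sample. The Introduction names attrition among the things a feasibility study is meant to teach. With few losses to learn from, throwing away part of the age information is a real, if small, waste.

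The second is the treatment factor. The sentence says procedure, whereas the section on data sources says treatment group. If procedure means the individual procedures, the losses are spread over eight levels, and the resulting table would say very little.

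**Working it through.** The plan gives no figure to reproduce. The Sample size section holds that "there is no requirement for a formal power calculation", and no precision is stated for the attrition analysis. The check therefore asks what each coding yields at the planned size.

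**Inputs from the article.** There are 20 + 20 = 40 patients. Losses, if the limit is just met, are 0.25 × 40 = 10, leaving 30 retained. There are three treatment groups containing 2 + 3 + 3 = 8 procedures.

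**Assumptions (not in the article).** Age is normally distributed. The difference in mean age between patients lost and retained is 0.5 to 1.0 SD. Tests are two-sided at 5%.

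**Age: large-sample efficiency.** Splitting a normal variable at its mean has relative efficiency 2/π = 0.637 against using the variable itself. So 40 × 0.637 = 25.5: for this question, 40 patients do the work of about 25.

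**Age: simulation at the planned size.** 8,000 samples of 40 per row; proportion with p < 0.05:

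| Lost | Age difference (SD) | t-test, continuous age | Split, chi-square (uncorrected) | Split, Fisher's exact |
|---|---|---|---|---|
| 10 | 0 | 0.05 | 0.06 | 0.02 |
| 10 | 0.5 | 0.27 | 0.20 | 0.11 |
| 10 | 0.8 | 0.57 | 0.42 | 0.28 |
| 10 | 1.0 | 0.76 | 0.57 | 0.42 |
| 4 | 0.8 | 0.31 | 0.25 | 0.12 |

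Repeat runs moved the 10-loss results by no more than about 0.02. The zero-difference row shows that Fisher's test runs well below its nominal 5%, so part of its shortfall comes from the test and not from the split. The chi-square column is the fairer comparison at 10 losses. At 4 losses, uncorrected chi-square rejects in about 7% of samples when there is no difference, so its 0.25 is somewhat flattering.

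**Age: what the continuous comparison delivers.** With 10 lost and 30 retained, the 95% half-width for the mean difference is 2.024 × √(1/10 + 1/30) = 2.024 × 0.365 = 0.74 SD. That is wide, but it is an estimate in years with an honest interval.

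**Treatment factor.**

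| Reading | Levels | Average patients per level | Average losses per level (10 lost) |
|---|---|---|---|
| Treatment group | 3 | 40/3 = 13.3 | 10/3 = 3.3 |
| Individual procedure | 8 | 40/8 = 5 | 10/8 = 1.25 |

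The averages assume an even spread, which is unlikely. Exact 95% intervals show what they mean: 3 lost of 13 gives 5% to 54%, and 1 lost of 5 gives 1% to 72%. Each procedure belongs to one group, so the group can always be recovered from the procedure. The finer variable loses nothing; it only thins the cells.

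**The case against.** The strongest reply is that this is a secondary, descriptive analysis in a feasibility trial that says it does not seek significant differences between groups, so power is the wrong yardstick. With about 10 losses, neither coding will settle who drops out; at 0.5 SD even continuous age detects the difference only about a quarter of the time. All of that stands, and it limits the weight of the point. It does not rescue the split: power serves here only as a measure of information, and a mean difference with an interval is also the better description.

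A reader might go further in four ways that the article does not support.

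- That using procedure in place of group discards information. It does not, because procedures are nested within groups.
- That procedure is not recorded. The article says that treatment group is obtained, not that nothing else is; eligibility is defined by procedure, and the data-collection figure is not visible in the text reviewed. Procedure may simply be loose wording for the group, in which case only a wording mismatch remains.
- That a result based on a mean split cannot be used later. Mean age will be reported, so the cut will be known; the result is less informative, not useless.
- That the power loss is as large as the comparison with Fisher's test suggests. No test is named, and chi-square shows a smaller loss.

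It is also fair to say that the sentence has other limits which this point does not cure: randomised arm is not among its factors, and type of informal caregiver applies only to the 20 intervention patients.

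**Conclusion.** The point holds as a minor one.

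The age split is explicit in the article, departs from the section's own handling of continuous variables, and has no stated reason. It costs about 36% of the information on age (1 − 0.637). At 10 losses and a difference of 0.5 to 1.0 SD, that is roughly a quarter of the detection probability with uncorrected chi-square (0.20/0.27 = 0.74; 0.57/0.76 = 0.75), and more with Fisher's test. These sizes rest on a normal age distribution and the assumed differences. A skewed age would change the 64%.

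The treatment term is a mismatch to be reconciled. Under the eight-procedure reading the harm is sparse cells, not lost information. Neither matter affects any feasibility criterion: the 25% limit on non-completion is counted the same way however age or treatment is coded.

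**What to change.** In the Data analysis section, drop the above-or-below-mean coding and state that age will be compared as a continuous variable between patients lost and retained, reported as a mean difference with a 95% confidence interval. Replace treatment procedure with the three-level treatment group (IHD, valve disease, arrhythmia), so that the term agrees with the section on health behaviors and health outcomes. Individual procedures can still be listed as counts if wanted.

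The cost is one sentence of analysis wording. It needs no new data, no extra patients and no change to the feasibility criteria.

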## Discussion

A social support intervention targeting patients treated for cardiac disease who experience loneliness has the potential to decrease the negative impact on health from cardiovascular reactivity and to promote condition management in the early rehabilitation period. Consequently, a social support intervention may diminish the inequality in health behavior and health outcomes we see in patients who experience loneliness. To date, the type of support, with the intensity and the duration of the intervention needed to bring about changes in the experience of loneliness and the process that mediates health behavior and health outcomes, is scarce. The present study will contribute with new knowledge on how to implement a feasible social support intervention and, furthermore, investigate the preliminary evidence on the effect on health behaviors and health outcomes. The added knowledge will inform the design of a potential upcoming RCT.

